### Power calculations, sample size and randomisation

In the absence of relevant data, we made the assumption that clinic use is equally distributed among the clinics. Each of the two population surveys will include around 4,000 participants from among a sample of 5,000, based on an estimated 80% response, and will give us approximately 500 people in each clinic (cluster). We adopted the use of the coefficient of variation as employed in similar study settings when a good intracluster variation is not available [24–26]. Data collected in Agincourt in 2010 provided a prevalence of moderate or greater cardiovascular risk of 36% and a coefficient of variation of 0.132 (error margin, 4.5% (0.132 ± 0.045)). Using these data, we calculated that we will have 88% power to detect a difference between an unchanged prevalence of risk of 36% in the control arm and a reduction to a prevalence of risk of 25% in the intervention arm. These calculations assume that the coefficient of variation will be similar in the two groups and that effects of the interventions are similar across clusters.

For each of the two population surveys, we will select a random sample of 5,000 people older than 18 years of age from the demographic surveillance database. The samples for the two surveys will be disproportionately stratified to ensure adequate representation of men and older people. This is necessary because (1) the population pyramid is heavily weighted toward younger people, and (2) there are fewer men than women amongst older adults due to labour migration [20] and the longer survival of women. Each sample will be independently selected, but we expect some overlap (estimated at around 4 to 500 individuals) between the two samples. All the individuals selected in both samples will be identifiable.

Randomisation of the eight clinics has been carried out at a public meeting attended by 38 members of the community, including clinic staff, lay members of clinic committees and members of a community advisory group. This was done to ensure that the community understands the purpose of the trial and that the clinic staff and wider community are confident that the randomisation was truly random. Eight pieces of paper with the names of the clinics were shown to attendees at the meeting, then put into sealed envelopes that were put in a box, which was shaken repeatedly before each envelope was chosen. The first clinic chosen was an intervention clinic, the second a control clinic and so forth.

### Baseline and end-of-intervention population surveys

All consenting participants in the surveys will have their blood pressure measured by trained field staff three times using an Omron automatic blood pressure machine (model M6W; Omron Healthcare, Lake Forest, IL, USA). The questionnaire takes around 30 minutes to administer, thus allowing both surveys to be completed within a 12-week period before the start of the intervention and at the end. Information will be collected regarding respondents’ use of primary care clinics in the past 12 months and their preferred clinic. Information on factors related to cardiovascular risk will be collected, and respondents will also be asked if they have had their blood pressure checked by a doctor or nurse in the past year, if they have ever been told they have hypertension and if they are using medication for hypertension (see Additional file 1 for a copy of the questionnaire).

### Data management and analysis

Quantitative data will be entered at the field site using double data entry. Personal identifiers will be encrypted once the data have been entered and cleaned. Encryption codes will be held securely in the MRC/Wits Agincourt Research Unit under the guardianship of the data manager. After completion of data collection, cleaning and encryption, the data files will be placed with other legacy data on the data warehouse server at the Agincourt research site.

All data sets derived from this project will be made publicly available within 1 year of the completion of data collection and cleaning. Secondary data users will submit a request for data access to the data custodians, appointed by the project principal investigators, by completing an online form. If the request falls within the bounds of appropriate data access requests as specified in the ‘MRC principles for access to, and use of, MRC funded research data’, then it will be approved. Collaboration with the original investigators in resulting publications will be encouraged.

A full analysis plan will be agreed upon with the management team and the trial steering committee before the analyses are begun. The primary analysis will be on intention to treat and will be carried out using STATA 13 software (College Station, TX, USA). Up to this point, clinic identifiers will be encrypted so that the primary analysis is carried out in blinded fashion regarding which clinics are the intervention clinics. In descriptive analyses, frequency distributions of categorical variables and summary measures of continuous variables will be reported. Baseline values in the intervention and usual care arms will be described.

To allow for confounding, the two-stage regression model will be used for analysis of the binary primary outcome ([27], pages 163--198). First, two logistic regression models for control and intervention clusters that include covariates will be fitted separately. Covariates in the two models will both be cluster-level factors (for example, clinic size) and aggregated individual-level factors (for example, sex and age). Second, observed and fitted values for each cluster will be compared by computing residuals. We expect relatively few missing values, especially for individual demographic data, because this trial is taking place in an established HDSS site with a rigorous quality assurance system.

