### Study outcomes

We aim to improve the management of hypertension with the goal of achieving a reduction in the proportion of the population with uncontrolled hypertension and a risk profile indicating at least moderate risk of cardiovascular disease. To do this, we aim to both increase the number of people receiving active management of their hypertension and improve the management of blood pressure in those patients already in active management. Because we hope to reach people not currently using the clinics, we have chosen to measure the outcome of the trial at the population level with the use of two population surveys (before and after the intervention).

The primary outcome we will measure is the difference in the change in intervention and control clinics between the two surveys in the proportion of the population who have uncontrolled hypertension and a risk profile indicating at least moderate risk of cardiovascular disease. The definition of this risk profile is shown in Table 1. It reflects the concepts in the 2011 South African guidelines [23], which call for a focus on people at moderate or greater cardiovascular risk. Although the guidelines require clinical diagnoses, we are limited by what is possible in a population survey, so, for the purposes of this trial, we will define the cardiovascular risk factors and associated clinical conditions as outlined in Table 2.

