### Trial status

Because of the design of the trial, it is difficult to define the status of recruitment. There are eight clinics, four of which receive the intervention and four which do not. They have been randomised, and the lay health workers have been in place since February to March 2014. Although the unit of randomisation is a clinic, the participants could most appropriately be considered to be the people using the clinics. They are participating or declining to participate by consenting to their data being linked to census data and by consenting to complete an exit questionnaire or permit their consultation to be observed as they attend the clinics. In that sense, we are just over halfway through recruitment (10 months of an 18-month period). The outcome is measured by population surveys at baseline and at the end of the intervention. If the people in those surveys are considered to be the participants, then we have recruited half (one survey). A separate group of around the same number of people will be asked to complete the survey at the end. The trial status was most recently updated 6 November 2014.

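### As worded, the two-stage primary analysis fits stage 1 separately in each arm, so with one residual per cluster the between-arm comparison carries no information on the intervention effect

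*Protocol article*

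**What the plan says.** Under Data management and analysis, the Protocol article states that "the two-stage regression model will be used for analysis of the binary primary outcome", so as to allow for confounding. It sets out two steps. Stage 1: "First, two logistic regression models for control and intervention clusters that include covariates will be fitted separately". Stage 2: "Second, observed and fitted values for each cluster will be compared by computing residuals". The covariates are described thus: "Covariates in the two models will both be cluster-level factors (for example, clinic size) and aggregated individual-level factors (for example, sex and age".

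No model fitted to both arms together is mentioned. Nor is there a step that applies one arm's fit to the other arm, or any other step that would yield an intervention effect.

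Under Study outcomes, the primary outcome is "the difference in the change in intervention and control clinics between the two surveys" in the proportion with uncontrolled hypertension and at least moderate cardiovascular risk. Trial status confirms the allocation: "There are eight clinics, four of which receive the intervention and four which do not".

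**The concern.** A two-stage residual analysis adjusts for covariates without removing the effect of interest. That requires the stage-1 fitted values to represent what each cluster would be expected to show if arm made no difference. One model over both arms, with no arm term, provides this, and the arm difference stays in the residuals. If each arm has its own model, the arm difference goes into the two intercepts. Stage 2 looks only at the residuals and so discards it.

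At stake is the trial's main result. A primary analysis run literally from these two sentences, with the cluster residuals then compared between arms, would show no difference whether the intervention helped, harmed or did nothing.

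**Working it through.** **Inputs.** From Power calculations, sample size and randomisation: about 500 people per cluster per survey, control prevalence 36%, intervention prevalence 25%, coefficient of variation k = 0.132. From Trial status: four clinics per arm. Assumption: two-sided 5% test, since the article states neither level nor sidedness.

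**The plan's own figure.** Convert k to an intracluster correlation at the control prevalence:
- ICC = k² × p0/(1 − p0) = 0.017424 × 0.36/0.64 = 0.0098
- design effect = 1 + 499 × 0.0098 = 5.89
- effective n per arm = 2,000/5.89 = 339.5
- power for 36% v 25% = 87.7%, which reproduces the stated 88%

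The inputs are therefore read as the authors meant them.

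**The algebra.** The maximum-likelihood equation for a logistic intercept is Σ(y − fitted) = 0 over the observations fitted. With one fit per arm it holds in each arm separately. The simplest case has equal clusters and no covariates:
- Separate fits: mean residual 36 − 36 = 0 in control and 25 − 25 = 0 in intervention. Difference 0.
- One fit over both arms: fitted value (36 + 25)/2 = 30.5. Mean residuals are +5.5 and −5.5. Difference −11 percentage points, the true effect.

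Adding covariates does not change the intercept equation.

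**Simulation, one survey.** 4 + 4 clusters, k = 0.132, individual sex and age as covariates, 600 runs per scenario, cluster residual (observed − expected)/n compared by t-test.

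| Clusters | True prevalence, control v intervention | Separate fits: mean difference; rejection | One fit, no arm term: mean difference; rejection |
|---|---|---|---|
| 500 each | 36% v 36% | 0; 0% | 0.001; 5.2% |
| 500 each | 36% v 25% | 0; 0% | −0.106; 79% |
| 500 each | 36% v 10% | 0; 0% | −0.260; 100% |
| 300 to 700 | 36% v 25% | −0.0002 (SD 0.009); 0% | −0.108; 79% |

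With equal clusters the separate-fit difference never exceeded about 6 × 10⁻¹⁶. With unequal clusters, dividing by n breaks the exact zero, but what remains is noise. Observed/expected ratios behave the same way: 1.00 with separate fits at 36% v 25%, against 0.71 with one fit.

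**Saturation.** If the covariates are clinic size, aggregated sex and aggregated age, each arm's model has 1 + 3 = 4 parameters for 4 clusters. It then reproduces every cluster's prevalence exactly. In a numerical check every cluster residual was about 10⁻¹².

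**Both surveys.** 500 per cluster per survey, 400 runs, each cluster's underlying deviation held constant between surveys (assumption), stage 1 fitted separately by arm.
- One residual per cluster: difference 0 to machine precision, with or without a survey term.
- Residual per cluster and survey, endline minus baseline, survey term in each arm's model: 0.
- The same without a survey term: −0.106, so the effect is recovered.

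**The case against.** The strongest objection is that the null result depends on how the two sentences are completed. The article does not say how the two surveys enter stage 1, and it describes no test between arms. If both surveys are pooled within each arm with no survey term, and a residual is taken per cluster and survey, the difference in change survives separate fitting. This stands as a limit: a reader might infer that the analysis cannot detect an effect under any reading, and the document does not support that. But the text speaks of residuals for each cluster, and the rescuing reading needs a step that is not written. Adding a survey term to each arm's model brings the zero back.

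The article also refers to a full protocol, a later analysis plan and textbook pages for the method. These are not at hand and may describe it correctly. The point therefore concerns the published wording, which gives a specific instruction that is wrong. It is not a complaint about missing detail.

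Two further inferences should be resisted.
- **Blinding.** A reader might think separate fits by arm conflict with the commitment that "clinic identifiers will be encrypted so that the primary analysis is carried out in blinded fashion regarding which clinics are the intervention clinics". They do not. Coded group labels are enough to fit by group, and any between-arm comparison of residuals needs the same grouping.
- **Power.** A reader might take the rejection rate of about 80% for the single fit as the power of the primary analysis. It comes from one survey and individual covariates, whereas the outcome is a difference in change. It shows only that the effect is recoverable. The zero under separate fits does not depend on those choices.

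**Conclusion.** Wrong as written. With stage 1 fitted separately by arm and one residual per cluster, the between-arm comparison of residuals carries no information on the intervention effect. Rejection is 0% at the planned 36% v 25%, and also at no effect and at 36% v 10%. The difference is exactly zero with equal cluster sizes and small noise with unequal ones. The conclusion assumes an intercept in each arm's model and a second stage that compares the cluster residuals between arms. It does not rest on the cited textbook or on the particular covariates simulated. Restricting the covariates to cluster-level or aggregated factors makes matters worse, since three of them exhaust the four clusters in an arm.

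**What to change.** Replace the two sentences with: 'Stage 1: one logistic regression on all individuals in all eight clusters and both surveys, with covariates and a survey term but no intervention term or survey-by-intervention term, and with few or no cluster-level covariates. Stage 2: for each cluster, compute the residual (observed minus expected, divided by n) in each survey, take endline minus baseline, and compare the four intervention values with the four control values by an unpaired t-test on 6 degrees of freedom, less one per cluster-level covariate.'

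Two details matter.
- **Residuals must be taken per survey and differenced.** One residual per cluster over both surveys averages an unaffected baseline with the endline and roughly halves the effect (−0.11/2 = −0.055). Simulation gave −0.053 with 25% rejection, against −0.107 for endline minus baseline from a single stage-1 model.
- **Cluster-level covariates are costly with eight clusters.** In the single-survey simulation with unequal clusters, adding clinic size alone to the single model moved the difference from −0.108 to −0.094 and rejection from 79% to 66%.

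The cost is two sentences in the protocol, carried into the analysis plan that is to be agreed before analysis starts. No new data or participants are needed.

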### Objectives and approach of the process evaluation

Given the importance of context, process and actors in the performance of the health care system [28], we cannot assume that the results of a health services randomised controlled trial will be transferable to other health care settings. We are therefore undertaking an extensive process evaluation and adopting a critical realism approach in which the predominant question is, what works for whom under what conditions? This approach acknowledges that preexisting health care system structures and processes affect, and are affected by, the intervention actors. In this evaluation, we aim to understand the causal processes of change. We will take a realist approach in the evaluation and explore the ‘mechanism’ by which the intervention has its effect [29]. The following are the objectives of the process evaluation:To examine how different aspects of the intervention function in the different clinics and the mechanisms by which the intervention affected or failed to affect the primary outcomeTo examine the extent to which the lay health workers and other clinic staff were able to work within the context of the complex adapting system of a primary health care facility, by learning, interacting and self-organising to establish sustained improvements in careTo explain how the implementation processes shaped the intervention and its functioningTo explain the role of the local context in determining outcomes

### Data collection and analysis for the process evaluation

In the study, we will use a range of qualitative methods, including interviews and observation. As is standard in qualitative methods, sampling will be purposive, designed to ensure representation of a range of views and inputs. Each clinic and its attending population will be treated as a single case, and a case study approach will be used to compare and contrast experiences in the four intervention clinics. Combining qualitative and quantitative data will allow the development of within- and across-clinic analyses to explain and interpret outcomes.

Data on the clinic use of individuals will be collected through a linkage system, where consenting patients’ clinical details will be linked to the demographic surveillance system. In addition, we will collect a range of quantitative and qualitative data for the process evaluation. Quantitative data will include brief exit interviews with patients who have attended the chronic disease clinic and have a diagnosis of hypertension. We will ask whether they had their blood pressure measured, what advice they were given, whether they have been given any medication and whether a return visit has been booked. Nursing staff in the clinics will be asked to complete a structured questionnaire on their motivation.

Qualitative data will include nonparticipant observation and repeated interviews with trial employees and health service staff, including clinic supervisors and subdistrict staff. Three purposively selected groups of people in the community will be followed up with in-depth interviews. There will be three observation visits to each clinic over the period of the intervention to observe the operation of the intervention activities, to describe patient pathways and to describe the health care system facilitators and barriers to hypertension care. Throughout the period of the intervention, the lay health workers and implementation manager will be interviewed monthly to capture information on the functioning of the intervention; the usefulness of the intervention activities; adaptations to the context, barriers and facilitators to care; the relationship between the various actors; and other changes taking place in the clinic.

Three cohorts of community members will be purposively identified for two in-depth interviews at around 3 to 5 months after the initiation of the trial and again at around 12 to 15 months. The first cohort will comprise both patients who only intermittently adhere to their medication and patients who have a high level of adherence. The second cohort will comprise individuals who report that they normally attend one of the clinics in the control arm of the study and report, when interviewed, that they have hypertension. The third cohort will include individuals with raised blood pressure upon measurement who either do not report that they have hypertension or who know their diagnosis but are not taking treatment, which maybe because they are not adherent to prescribed treatment or because they have not been prescribed any treatment.

### Economic evaluation

A partial economic evaluation will be undertaken alongside the trial. As there is potential for multiple key outcomes that cannot be aggregated into a single outcome, a cost–consequence analysis will be the primary economic study undertaken to obtain an array of output measures alongside the costs. This will enable us to show the trade-offs associated with each scenario. We will collect patient-level costing data to examine the cost implication for the public sector as the funder of primary health care, as well as costs to the patient of participating in the intervention. Salary and training costs for the lay health workers and experienced nurse, as well as communication costs (such as telephone calls, SMS) will be included in the intervention cost, as well as the cost of additional services delivered by the health facility. Costs associated with the government’s ICDM programme, which is common across both intervention and comparator sites, will not be included in the analysis. Costs (in South African rand) will be collected over the course of the study, and all prices will be inflation-adjusted to the final year of the study. Nonparametric bootstrapping will be used to assess the effect of variation in patient-level outcomes on the costing results.

## Discussion

We have faced a number of challenges in designing this trial. We already knew that at least half of the people with hypertension were not aware of their condition and therefore were not receiving regular treatment [30], and we wanted to target those people as well as the people already in the clinic system. Also, until very recently, no clinic records of individual patients were kept, and the new recordkeeping system was of variable quality. It was apparent, therefore, that a simple clinic record–based measure would not be possible as the primary outcome. We therefore decided to use baseline and end-of-intervention population surveys to measure change. This created a further challenge of carrying out a large-enough survey to achieve adequate power quickly enough to obtain a realistic baseline measure.

Because the intervention involved extra resources for some clinics, we were concerned that the process of randomising the clinics could lead to suspicion about whether it was truly random and thereby create negative feelings. We therefore held a public meeting at which the randomisation took place.

To ensure that the intervention achieves the best possible outcome, the implementation manager will aim to increase clinic staff’s awareness of patient constraints, adapt activities to suit the local context and obtain local commitment. This engagement may change the local clinic context, and context and intervention are likely to coevolve. As a result, it is not realistic to attempt to maintain rigid adherence to a predetermined protocol. It is therefore important to document the evolution of the intervention, which is the reason for the extensive process evaluation. At the same time, however, to maximise the external validity of the study, it is important to keep the intervention realistically close to the type of intervention that might be feasible in a low- or middle-income country. This has led to two important dilemmas for the team. First is the extent to which findings from the process evaluation should be fed back to the implementation manager and lay health workers, as standard government policy implementation does not receive the benefit of ‘real-time’ evaluation to enable improvement. Second is the extent to which the trial team should intervene to provide extra resources where the lack of resources is preventing the effective functioning of the lay health workers. In regard to both of these dilemmas, we are regularly making day-to-day decisions, balancing the need for external validity with the practicalities of getting an intervention to run in a challenging environment. All these decisions are being carefully recorded so that we can provide a fully informed report at the end of the trial.

